## Abstract

**Background:**

Early interventions benefit the mental health, academic performance and productivity of children and adolescents throughout their life. The present study protocol will evaluate the effectiveness of the Elos 2.0 Programme, which is a version adapted for Brazil by the Ministry of Health, in reducing problem behaviours (e.g., disruptiveness, aggressivity and shyness) and promoting social skills in the school context in children 6 to 10 years of age. The Elos Programme is based on the Good Behaviour Game*,* which is widely used and prevents and/or reduces students’ disruptive behaviours by establishing cooperation contingencies.

**Method:**

A cluster-randomized controlled trial will be performed in 30 schools in three cities (15 controls and 15 in the experimental group), with a total of 3800 children participating in the test (1900 in the control group and 1900 in the intervention group). Data will be collected by having teachers in the control and experimental classes complete the Teacher Observation of Classroom Adaptation (TOCA) questionnaire, which is an instrument used to observe children’s behaviour in the classroom. We will collect data before and after the intervention period in the same year. Due to the hierarchical structure of the data, multilevel analysis will be performed to detect simultaneous differences in prevalence over time and across groups to control for sociodemographic variables.

**Discussion:**

The current study will examine the effectiveness of the Elos 2.0 Programme in reducing problem behaviours (e.g., disruptiveness, aggressivity and shyness) and promoting social skills in the school context. The findings of this school-based prevention programme for children will influence the development and implementation of similar programmes for schools and educational policymakers by identifying mechanisms that are central to achieving positive outcomes for participants.

**Trial registration:**

Registry of Clinical Trials of the Ministry of Health RBR-86c6jp. Registered February 2, 2019

**Supplementary Information:**

The online version contains supplementary material available at 10.1186/s13063-021-05408-0.

## Administrative information

The order of the items was modified to group similar items (see http://www.equator-network.org/reporting-guidelines/spirit-2013-statement-defining-standard-protocol-items-for-clinical-trials/).

## Introduction

### Background and rationale {6a}

One fifth of children worldwide are affected by emotional and behavioural problems. The disease burden associated with these mental disorders includes the costs of their reduced chance of completing basic education, lack of social cohesion and reduced ability to cope with future adversities, which are also associated with negative outcomes later in life if no preventive measures are taken [1–4].

Interventions in childhood generally aim to promote the overall development of children. However, evidence shows that these early interventions also benefit the short- and long-term mental health of children and adolescents [2, 5]. Studies examining the effects of preventive interventions in educational or family contexts on children and adolescents with some risk factors showed positive results in reducing the incidence and/or progression of mental disorders throughout life [6–9].

The Good Behaviour Game (GBG) is one of the most effective programmes to promote mental health in children and adolescents and prevent and/or reduce students’ disruptive behaviours via the establishment of cooperation contingencies [10, 11]. The GBG aims to equip teachers with behaviour management strategies in the classroom to reduce aggressive or disruptive behaviours, shyness and/or social isolation. These behaviours are risk factors for future negative outcomes in mental health, such as anxiety and depression [12].

The GBG procedure is divided into three stages. In the first stage, students from the same classroom are divided into heterogeneous teams according to gender, academic performance and behaviour pattern (problems and prosocial). The teachers presents four rules that must be followed during GBG: (1) follow the instructions for activities, (2) follow the voice levels (silence, whisper, group voice, presentation or street voice), (3) follow the arrangement of seats (remain seated, stand and walk as agreed or stand and walk freely) and (4) be kind. The rules are illustrated on posters posted in classrooms as the game takes place. To play GBG, teachers must select pedagogical activities according to the school curriculum that students can perform autonomously, such as exercises and artistic activities. Therefore, the teacher does not offer pedagogical support to the students during the GBG to promote autonomy and group cooperation.

The teacher observes the students during the GBG, and if they break the rules, he/she (1) describes the inappropriate behaviour to the classroom in a neutral tone of voice immediately after the occurrence, (2) records the rule break on the blackboard and assigns one point and (3) praises the other students who are following the rules.

At the end of GBG, teams with a maximum of five points win the game. Notably, all of the teams can win the game, which avoids the existence of competition between children. The teachers announce the winning teams but do not mention the losing teams. The winning teams and students receive prizes, including tangible immediate reinforcers, such as stamps in a notebook and coloured pencils, and intangible immediate reinforcers, such as praise and applause. There is also a score for teams that win games over a period of time, such as a week, for the distribution of delayed reinforcers. Briefly, the awards and recognitions for following the rules occur in three ways: reinforcement to the students immediately after the game, reinforcement to the team immediately after the game and reinforcement to the team at the end of each week of the game [13–15].

Since its inception, the GBG has been implemented in several countries, including the USA [13], Sudan [16], the UK [17] and Belgium [18, 19]. Because the GBG has been widely used, it is an evidence-based practice with proven effectiveness for the (a) reduction of disruptive and aggressive behaviours in the school context [11], (b) prevention of the use and abuse of psychoactive substances [12, 20, 21], (c) prevention of suicide ideation and attempts [20, 22] and (d) prevention of the development of violent behaviour and antisocial personality disorder in adulthood [23].

The integration of GBG in the school curriculum is an innovative proposal that could facilitate the teaching and learning processes [24]. Because it improves interactions between teachers and students, the GBG likely improves students’ mental health outcomes and enhances their academic abilities. Positive teacher-student social interactions are associated with better academic results because the teacher builds a welcoming environment via the use of social reinforcers, such as acknowledgements, praise and descriptions of appropriate behaviours [25–27]. Good academic results in children and adolescents, especially results related to reading, contribute to good mental health indicators, such as empathy [28], rationality and creativity [29], social well-being, well-defined daily routine and self-satisfaction with life [30, 31].

Previous studies demonstrated that teacher-specific characteristics, such as years of experience, education, mental health and a sense of self-efficacy, tended to impact social interactions and school climate [25, 32, 33]. These characteristics are relevant because the teacher profile may attenuate problem behaviours in students by promoting academic success and social skills, which would produce a compensatory effect on the maladaptive behaviour losses [34–36].

The GBG programme was adapted in Brazil in 2013 for children between 6 and 10 years of age and named “Programa Elos: construindo coletivos” (Elos Programme: constructing collectives). The objective of the programme is to promote cooperative and democratic interactions between teachers and students [37]. By changing interactions that are considered maladaptive in the classroom context, the programme intends to promote mental health and prevent and/or reduce problem behaviours (e.g., disruptiveness, aggressivity and shyness). The purpose of the Elos Programme is also to promote early protective factors to eliminate or minimize the risks of drug use and abuse in the long term. In other words, it is a tool for the prevention of the use and abuse of psychoactive substances, which was shown in other studies of GBG [12, 23].

The cultural adaptation and implementation of the Elos Programme pre-pilot occurred in four Brazilian municipalities in 2013. The programme was implemented in other schools in 17 municipalities on a pilot basis in subsequent years (2014 and 2015) [38]. However, randomized controlled trials with a control group to test the effectiveness of this programme in Brazil were not performed. Therefore, the programme materials were revised, and the updated version of the programme was named Elos 2.0.

To disseminate this tool on a national scale, it is essential to test the effectiveness of the programme when it is adapted to our culture, as recommended by the PROMISE (Providing mental health promotion training guidelines and training resources for healthcare professionals) project [39]*.*

## Objectives {7}

The main objective of this cluster-randomized controlled trial is to evaluate the effectiveness of the Elos 2.0 Programme, which is a version adapted to Brazil for proposed implementation by the Ministry of Health, in the reduction of problem behaviours and promotion of prosocial behaviours in children in public schools. All outcomes are measured at the level of the individual child. Our main hypothesis is that students between the first and fourth years of elementary school who are exposed to the Elos 2.0 programme for 5 months will have a lower frequency of problem behaviours (e.g., disruptiveness, aggressivity and shyness) and better prosocial behaviours compared to the control group.

## Trial design {8}

A cluster-randomized controlled superiority trial will be performed in 30 schools in three cities (15 controls and 15 in the experimental group), with a total of 3800 children participating in the test (1900 in the control group and 1900 in the intervention group). This study is a randomized controlled trial with two parallel groups (intervention and control) of students aged 6 to 10 years and enrolled in the first to fourth year of elementary education in public schools in the cities of Fortaleza, Eusébio and São Paulo, which are located in the states of Ceará and São Paulo. The ratio of intended numbers of participants in each of the comparison groups is 1:1. The control group receives treatment as usual in Brazil, i.e., no behavioural intervention at the school.

## Methods: participants, interventions and outcomes

### Study setting {9}

Public schools with at least one class of each grade (first to fourth grade) will be included. Schools enrolled in the trial will not offer programmes and/or activities for the prevention of drug use and abuse or the promotion of mental health in 2019. Collaboration with the Municipal and State Departments of Health and Education, which is essential for the implementation and evaluation of the Elos 2.0 Programme in schools, will be led by the National Coordination of Mental Health, Alcohol and Other Drugs of the Ministry of Health (responsible for implementing the programme).

### Eligibility criteria {10}

Schools will be included in the study according to the following criteria: (1) being a public school and (2) having at least one class of each grade (first to fourth grade) and all children in these grades will be included in the trial.

### Who will take informed consent? {26a}

Study coordinators and trained interviewers will introduce the trial to participants, who will attend a seminar on the main aspects of the trial. Participants will also receive information sheets. Participants may have an informed discussion with the study coordinator and staff. Trained interviewers will obtain written consent from participants who are willing to participate in the trial. Information sheets and consent forms will be provided for all participants involved in the trial, but these forms were amended accordingly to provide separate information sheets and consent forms, which are more suitable for children. We will obtain consent to participate in the study from the schools’ principals, teachers, students and parents. The intervention will be part of the school curriculum, and it will be mandatory for all students in the active school group.

### Additional consent provisions for the collection and use of participant data and biological specimens {26b}

Not applicable. This trial does not include the collection or derivation of data for purposes that are separate from the main objective of study.

## Interventions

### Explanation for the choice of comparators {6b}

Among the schools selected to participate in the study, a second simple randomized selection will define the control and experimental schools at a ratio of 1:1 control and experimental schools per municipality. The selected comparison group is treatment as usual, which means no behavioural interventions delivered in the control schools. This is a suitable comparator, as it is the standard experience of schoolchildren in Brazil. Public schools for children in Brazil do not usually receive interventions to improve behavioural skills.

### Intervention description {11a}

Teachers will present four rules to be followed by the student teams during the Elos Game 2.0: (1) follow the instructions for the activities, (2) adhere to the voice levels (silence, whispering, group voice, presentation or street voice), (3) comply with assigned positions (remain seated, stand up and walk as arranged or stand up and walk freely) and (4) be kind. The rules will be the same for all teachers and will be illustrated on posters that will be posted in classrooms. To play the Elos Game, teachers should select pedagogical activities that are consistent with the school curriculum and can be performed autonomously.

For each experimental school, all students from the first to fourth grades will participate in the Elos Programme as a regular school activity, and the school will designate one teacher per class to receive training on the programme.

### Criteria for discontinuing or modifying allocated interventions {11b}

The assigned study intervention will be offered equally to all classes enrolled in the intervention group. If any teacher or student refuses the invitation to participate in the trial or refuses to discuss the process of implementation, they will not be included in the study, since agreement to participate is an inclusion criterion. If teacher refuses the invitation to participate in the trial, we will reallocate other school for the intervention group following the random drawing from the list. Teachers and students who started the trial but decide to drop the study after baseline assessment they will provide follow-up data.

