## Assignment of interventions: allocation

### Sequence generation {16a}

The allocation of schools (1:1) to the control or intervention group will be performed via simple random drawing from the list of the Anísio Teixeira National Institute of Educational Studies and Research (INEP, its acronym in Portuguese), which includes all Brazilian schools separated by city. Randomization will be performed using a quantitative methodology in PASS 15 Efron’s biased coin (two treatments, equal sample sizes). The target sample sizes are the same for both groups. To achieve a longitudinal balance between groups, the algorithm dynamically changes the group assignment probabilities.

The unit of randomization between groups is the schools and not the classes. Therefore, there will be no control classes in an experimental school and vice versa to avoid sample contamination. Agreement to participate in the study was received from the schools before randomization.

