### Methods in the analysis to handle protocol non-adherence and any statistical methods to handle missing data {20c}

We will compose a letter-number code for each subject based on the school and personal information to maintain confidentiality and blinding in the data analyses. We will perform double data entry in the dataset and multiple imputation to handle missing data from the follow-up of participants which do not refuse to participate at the beginning or do not decline to perform the implementation. Missing data in the follow-up could occur if the child misses school on the data collection or if the child changes of school or city, which is likely to occur in any longitudinal drawing. Two different techniques will be used and contrasted: multiple imputation and the complier-average causal effect (CACE), which provide a form of sensitivity analysis of our intervention effects [45, 46]. CACE will be calculated by using data from the fidelity forms answered weekly by the teachers. Non-adherence will not consider the classroom where the teacher did not complete the program or have not delivery at least 50% sessions of Elos.

Multiple imputation operates under the assumption that the underlying missing mechanism is *missing at random* (MAR) and here multiple imputation will be carried out using Bayes estimation of an unrestricted variance-covariance model, where all of the main assessments of baseline sociodemographic and school features in the data set will be assumed as dependent variables. The variables with missing values will be included in the imputation step. The number of data sets to be imputed will depend on the fraction of missing information [42]. In case of missing data on child primary outcome (follow-up), they will be imputed. We do not expect child missing data at baseline outcome, but situation as loss of questionnaires, parents giving up of the children participations might happen requiring imputation of baseline primary outcome assessment. Multiple imputation is in accordance with intention-to-treat paradigm (ITT) broadly advocated by CONSORT [44]. We will perform an analysis using the ITT principle (all participants will be analysed as randomized, irrespective of whether they received the intervention in the intervention group) with observed data only, and a further ITT analysis using observed and imputed data. The primary analysis will be with the ITT using observed data only.

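### Read literally, the teacher-refusal rule places a replacement school straight into the intervention group, outside the randomisation on which the primary analysis relies

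*Protocol article*

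**What the plan says.** All references are to the protocol article.

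- **{11b}, on modifying allocated interventions.** When a teacher declines the invitation, "we will reallocate other school for the intervention group following the random drawing from the list". Neither this section nor any other gives control schools an equivalent rule. The section also says that if a teacher or student declines the invitation or "refuses to discuss the process of implementation, they will not be included in the study", because agreement is an inclusion criterion. It ends by requiring follow-up data from teachers and students who withdraw after the baseline assessment.
- **Recruitment {15}.** A separate rule replaces schools that refuse at recruitment by random selection of 10% more schools. It is not tied to an arm.
- **Sequence generation {16a}.** "The unit of randomization between groups is the schools and not the classes", and "Agreement to participate in the study was received from the schools before randomization".
- **Concealment {16b} and Implementation {16c}.** A city's schools are randomised together once that city's recruitment is complete. Recruiting staff do not know earlier allocations. All consenting, eligible schools are randomised.
- **Non-adherence and missing data {20c}.** Under intention to treat, "all participants will be analysed as randomized, irrespective of whether they received the intervention in the intervention group". "The primary analysis will be with the ITT using observed data only".

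**The concern.** A school can be replaced in the intervention group only if that group already exists. The draw from the list then decides which school comes in, but not which arm it joins, since the arm is fixed as Elos. Such a school was never randomised, while the school it displaces was. An analysis as randomised cannot accommodate both facts.

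The clause on refusing to discuss implementation points the same way. Control schools receive no intervention, so this ground for exclusion is likely to arise only in the intervention arm.

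At stake is the comparability of the arms. Teachers are not blinded {17a} and they complete the TOCA-C {12}. Dropping schools with reluctant teachers from one arm therefore selects on the people who supply the outcome.

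**Working it through.** **1. Could the rule apply only before randomisation?**

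- The agreement that {16a} places before randomisation is that of the schools. Teachers are not mentioned there.
- {11a} has each experimental school designate one teacher per class for training, which suggests that these teachers are named after the arm is known.
- {15} already covers refusal at recruitment without reference to arm. If {11b} covered the same stage it would be redundant, and its mention of the intervention group would be wrong.
- {16b} and {16c} provide no route for adding a school to one arm after a city has been randomised.

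Either the rule acts after allocation and conflicts with {16a} to {16c} and {20c}, or it acts before allocation and is misworded. Both readings call for a correction.

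**2. The plan's own power figure {14}.** Inputs: difference 0.25, SD 0.80, ICC 0.05, mean cluster size 100, coefficient of variation 0.70, and 1500 children per arm (15 clusters read as per arm, two-sided 0.05 assumed).

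- L = 100 × 0.05 / (100 × 0.05 + 0.95) = 0.840
- Relative efficiency = 1 − 0.70² × 0.840 × 0.160 = 0.934
- Design effect = (1 + 99 × 0.05) / 0.934 = 6.37
- Standard error = 0.80 × √(6.37 × 2/1500) = 0.0737
- Power = Φ(0.25/0.0737 − 1.96) = 92.4%, which agrees with the stated 92%

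A more conservative design effect, 1 + ((0.70² + 1) × 100 − 1) × 0.05 = 8.40, gives 84.0%. The first version is used below because it reproduces the plan. A one-for-one swap leaves the number of schools and the power unchanged, so the issue is bias and not precision.

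**3. Illustrative bias.** If r of 15 intervention schools are swapped, and replacements differ from refusers by g TOCA points, the shift is (r/15) × g. The documents give neither r nor g, so both are assumptions.

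- Between-school SD = 0.80 × √0.05 = 0.179. Take g equal to this.
- r = 2: 2/15 × 0.179 = 0.024, or 10% of 0.25
- r = 4: 4/15 × 0.179 = 0.048, or 19% of 0.25
- In standard errors: 0.024/0.0737 = 0.3 and 0.048/0.0737 = 0.65

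Over a wider grid, r = 1 to 3 and g = 0.1 to 0.4, the shift is 0.007 to 0.080 (3% to 32% of the target) and the two-sided type I error is 0.051 to 0.192.

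On how 2 to 4 swaps could arise: each school has at least four classes {10}. If each of four teachers independently had a 5% chance of refusing (assumption), and any one refusal triggered a swap, then 1 − 0.95⁴ = 18.5% of schools would be affected, or 2.8 of 15.

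These figures take no account of adjustment for the baseline outcome.

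**4. Cost of keeping refusing schools.** With r zero-effect schools retained, the difference is 0.25 × (15 − r)/15, at standard error 0.0737:

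| r | difference | power |
|---|---|---|
| 0 | 0.250 | 92.4% |
| 1 | 0.233 | 88.6% |
| 2 | 0.217 | 83.6% |
| 3 | 0.200 | 77.4% |

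**The case against.** The strongest reply is that the rule concerns recruitment and is only badly worded. Its trigger is refusal of an invitation, and {15} uses invitation for recruitment. The section itself says of refusers that "they will not be included in the study, since agreement to participate is an inclusion criterion", which is screening language. The timeline {13} lists consent ahead of randomisation, both in the same pre-trial column. {26a} seeks consent from principals, teachers, students and parents, and {16c} randomises only consenting schools. This stands to the extent that the timing is ambiguous, and the documents do not establish that swaps after randomisation are intended or have occurred. It does not rescue the wording, for the reasons in the first step of the working.

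A reader might infer more than the text supports:

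- **That all the exclusions act in one arm only.** General refusal applies to any teacher or student, and control teachers must also agree because they complete the TOCA-C. Only the school replacement and the implementation clause look one-sided.
- **That control schools are unselected.** They too agreed before randomisation.
- **That refusers are simply lost.** Those who withdraw after baseline must be followed up, and {20c} contrasts a complier-average analysis with intention to treat. The exposed window runs at most from allocation to baseline.
- **That no analysis could help.** The model in {20a} includes the baseline outcome and adds covariates that are clearly unbalanced. This may remove part of the bias, although it cannot be relied on to remove differences in teacher motivation or in how ratings change.
- **That the bias must favour Elos.** Teachers with well-behaved classes might decline because they see no need, so the direction is unknown.

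**Conclusion.** The concern holds as a conflict in the text with a real risk to the randomised comparison. Taken literally, {11b} assigns a replacement school to the intervention without randomising it and has no control counterpart. That cannot be reconciled with {16a} to {16c} or with the primary analysis in {20c}. On the milder reading the sentence is still wrong and needs correcting.

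The size of any bias cannot be determined from the documents. The shift of 0.024 to 0.048 (10% to 19% of the target) rests on assumed values of 2 to 4 swaps and a gap of one between-school SD, before baseline adjustment. The stated power is not in dispute. The correction is warranted because the rule touches the basis of the primary comparison and is cheap to change.

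**What to change.** Reconcile {11b}, {15}, {16a} to {16c} and {20c} as follows.

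1. In every school, obtain agreement from the principal and from each designated teacher before that school's city is randomised. Teachers must therefore be designated in all schools, not only in those later allocated to Elos.
2. Allow a refusing school to be replaced only before its city is randomised, by the arm-neutral rule in {15}.
3. In {11b}, delete the reference to the intervention group and the exclusion of those who refuse after allocation.
4. Once a school is randomised, follow and analyse it and its consented children in the assigned arm, whether or not Elos is delivered. This extends the existing follow-up rule for withdrawals after baseline back to the point of allocation.

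The cost is a change of wording, an earlier consent step for teachers, and teacher designation in schools that may become controls. There is also a statistical cost, which may not be small: an intervention school that refuses after allocation stays in the analysis and dilutes the effect. One, two or three such schools with no effect would bring power to about 89%, 84% or 77%. Securing teacher agreement before allocation is meant to make such cases rare.
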